## Methods and design

### Design

This is a parallel, two-arm, randomised, open-label, multicentre (13 sites in France), prospective study comparing the superiority and safety of an algorithm-guided rituximab regimen with the standard regimen in adult patients with membranous nephropathy. The study will last 7 years, with a 6-year enrolment period and 1 year of follow-up. An overview of the study is shown in figure 1.

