### Randomisation

After signing the informed consent and completing the screening visit to validate the inclusion criteria, participants will be randomised to one of the two treatment arms: (1) standard rituximab regimen and (2) algorithm-guided rituximab regimen. Centralised block randomisation will be balanced (1:1). Randomisation will be integrated into the electronic case report form (e-CRF) specifically designed for the study using the Research Electronic Data Capture (RedCap) software. Entering their personal access details to log in, the investigators will provide the necessary patient information (ie, the first letter of their first and last name and their month and year of birth) for random assignment to treatment using an online randomisation module (RedCap). The treatment group and inclusion number for the patient will be relayed to the investigator and the central laboratory team. The patient’s trial records will then be created automatically, allowing data to be entered.

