### Evaluation criteria

The primary endpoint is the clinical remission 6 months after the first rituximab infusion. Clinical remission is defined as a composite criterion, combining according to KDIGO guidelines: (1) complete clinical remission, defined as urinary protein/creatinine ratio (UPCR) <0.3 g/g in a morning spot urine sample and serum albumin >30 g/L and (2) partial clinical remission, defined as UPCR <3.5 g/g with a decrease >50% from baseline (ie, first rituximab infusion) and improvement or normalisation of serum albumin.

Secondary endpoints include complete clinical remission at month 12; partial clinical remission at month 12; immunological remission (ie, negative antibody titre by ELISA or negative indirect immunofluorescence) at month 3, month 6, month 9 and month 12; changes in proteinuria and albuminuria from baseline to month 3, month 6, month 9 and month 12; changes in serum creatinine and CKD-EPI estimated glomerular filtration rate from baseline to month 3, month 6, month 9 and month 12; changes in anti-PLA2R1 antibody ELISA titre from baseline to month 3, month 6, month 9 and month 12 (patients with PLA2R1-associated membranous nephropathy only); occurrence of anti-rituximab antibodies at month 3, month 6, month 9 and month 12; residual serum rituximab level at month 3 after the first rituximab infusion; recording adverse events related to treatment during study follow-up; changes in lymphocyte counts: B cells (CD19, transitional, mature and memory) and T cells (CD3, CD4, CD8 and T-Reg); changes in non-immunosuppressive antiproteinuric treatment during study follow-up; assessment of clinician satisfaction with the algorithm used to calculate the risk of rituximab underdosing (in the experimental group only); predictive rate (%) of the algorithm for rituximab underdosing in the control group; pharmacokinetics in all patients with serum creatinine and serum albumin levels, weight, anti-PLA2R1 and rituximab level at day 0, day 15, day 30, day 45, month 3 and month 6; and plasma cytokine levels after non-specific stimulation of innate and adaptive immunity cells in pg/mL (interferon (IFN)-γ, IFN-α, interleukin (IL)-12p70, IL-17A, IL-4, IL-5, IL-10, IL-1 and IL-6) at day 0 and month 6.

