In case of a statistically significant result at an interim analysis (p value under significance level), the independent committee will decide the termination of the trial (the interim analysis becomes the main analysis). Any retreatment with immunosuppressive therapy (including rituximab) not planned in the protocol before the end of the study at month 12 will be considered a treatment failure (ie, absence of remission). The statistical tests used, parametric or non-parametric, will consider the total number of patients and the distribution of the variables collected.

For secondary objectives, rates of complete and partial clinical remission at month 12 will be compared using a one-tailed test for the difference between two binomial proportions. Changes in biological samples at 3, 6, 9 and 12 months will be evaluated first by analysis of variance if the normal distribution hypothesis is met and second by a paired Student’s t-test or non-parametric Wilcoxon’s S-rank test, as recommended. For longitudinal analyses, secondary outcomes will be analysed using a linear mixed model to account for repeated measures, including fixed effects for time and intercept random effects for patients. The variables of interest and adjustment will be primarily age and sex, given the total number of patients and the distribution of the variables collected.

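### As worded, the mixed model for the continuous secondary outcomes names time, age and sex but not treatment arm, so it describes a trajectory pooled over both regimens

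*Protocol article*

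**What the plan says.** The Design section of the protocol article describes a two-arm randomised study "comparing the superiority and safety of an algorithm-guided rituximab regimen with the standard regimen".

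The Evaluation criteria section lists continuous secondary endpoints measured repeatedly, for example "changes in proteinuria and albuminuria from baseline to month 3, month 6, month 9 and month 12". Serum creatinine, eGFR and anti-PLA2R1 titre follow the same schedule, the last only in patients with PLA2R1-associated disease. Changes in lymphocyte counts are listed without visit times.

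The last paragraph of Statistical methods gives the secondary analyses:

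- Complete and partial remission rates at month 12 "will be compared using a one-tailed test for the difference between two binomial proportions".
- Changes in biological samples are evaluated first by an analysis of variance, with no factor named, and second "by a paired Student’s t-test or non-parametric Wilcoxon’s S-rank test, as recommended".
- Longitudinal outcomes are analysed with "a linear mixed model to account for repeated measures, including fixed effects for time and intercept random effects for patients".
- On covariates: "The variables of interest and adjustment will be primarily age and sex". The sentence goes on to refer to the number of patients and the distribution of the variables.

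**The concern.** In a randomised comparison the variable of interest is the allocated arm, and age and sex can only be adjustment variables. The sentence on covariates puts age and sex in both roles, and the model sentence before it names only time and a patient intercept.

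Both arms receive rituximab, so a time effect pooled over arms shows only that treated patients change. It cannot show whether algorithm-guided dosing changed proteinuria, renal function or antibody titre more than two 1 g doses did. The paired tests have the same limit. Run separately in each arm, they would invite the reader to set a significant change in one arm against a non-significant change in the other, and that is not a test of the difference.

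At stake is the supporting evidence from the continuous outcomes. The trial is open-label with three interim analyses, so it is better to fix the treatment contrast in writing now than to settle it once data are available.

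**Working it through.** The plan gives no figure for this point. The 130 patients and the interim significance levels derive from month-6 remission proportions (75% versus 50%) and do not involve the mixed model. The check is a reading of the model's terms.

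**Inputs.** Named fixed effects: time. Named random effect: patient intercept. Named variables of interest and adjustment: age and sex (all from Statistical methods). Time points: baseline and months 3, 6, 9 and 12 (Evaluation criteria). Allocation 1:1 (Randomisation).

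**1. Model with the named terms only.** For patient *i* at visit *m*:

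y(i,m) = β0 + θ(m) + β1·age(i) + β2·sex(i) + u(i) + e(i,m), with θ(0) = 0.

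Fixed-effect parameters: 1 intercept + 4 time + 1 age + 1 sex = 7. None compares the arms.

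**2. Same model with arm and arm-by-time.** Add γ·arm(i) + λ(m)·arm(i), with λ(0) = 0. This gives 7 + 1 + 4 = 12 parameters. The four λ(m) are the between-regimen differences in change from baseline at months 3, 6, 9 and 12.

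**3. What θ(m) means without arm.** Let δC(m) and δE(m) be the mean changes from baseline in the control and experimental arms. With 1:1 allocation and complete data, θ(m) = [δC(m) + δE(m)] / 2. Any pair of arm means with the same average gives the same θ(m), so δE(m) − δC(m) cannot be recovered from it.

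**4. Illustration on simulated data** (130 patients, 65 per arm, invented effects; it shows the algebra and nothing about this trial). Both models were fitted to the same data.

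| Month | θ without arm | δC | λ | δC + λ/2 |
|---|---|---|---|---|
| 6 | −0.6727 | −0.7462 | 0.1471 | −0.7462 + 0.0736 = −0.6727 (unrounded inputs) |
| 12 | −1.3645 | −1.1870 | −0.3551 | −1.1870 − 0.1775 = −1.3645 |

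The model without arm returns the average of the two arms exactly. The difference λ appears only in the second model.

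**5. The neighbouring sentences, side by side.**

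| Outcome | Stated analysis | Between-arm comparison stated? |
|---|---|---|
| Month-12 remission | difference between two proportions | yes |
| Continuous changes | analysis of variance, factor not named | unclear |
| Continuous changes | paired t or Wilcoxon signed-rank test | no, within patient |
| Continuous, longitudinal | mixed model: time, patient intercept, age, sex | not named |

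So the paragraph states a between-arm comparison for the binary outcomes and names arm in none of the analyses of the continuous ones.

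**The case against.** The strongest reply is that the lists are open. The model sentence says *including* and the covariate sentence says *primarily*, and neither excludes arm. The count of 7 parameters with no arm contrast follows only if the list is taken as complete. The text falls under secondary objectives in a trial whose stated aim is comparative, so a reader may fairly take the randomised factor as implied. Interest and adjustment are named together, and the remark on patient numbers suggests that the authors were limiting covariates rather than replacing arm. The analysis of variance could be the between-arm step. A condensed article commonly leaves the full list of model terms to the analysis plan.

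Much of this stands. A reader might infer that the plan estimates no difference between the regimens on any continuous outcome, or that five endpoints at four visits make 20 comparisons with no planned estimate. The documents do not support either: the wording is not exhaustive, and the analysis of variance may supply a comparison. The count also measures no bias or loss of power.

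The reply does not remove the point. The article does not simply leave the terms unstated. It names age and sex as variables of interest, and it specifies within-patient tests where a contrast between regimens is needed. An analysis plan that followed the text literally would miss the randomised comparison in this model.

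**Conclusion.** The point holds as a moderate issue limited to the continuous longitudinal secondary outcomes. None of the analyses described for them names treatment arm, and with the named terms alone the mixed model yields a trajectory pooled over arms. This rests on reading the named terms literally. If the full protocol or analysis plan already includes arm and arm-by-time, only the article's wording is at fault.

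The month-6 primary endpoint, the month-12 remission comparison, the interim boundaries and the sample size of 130 are unaffected. Conduct and data collection do not change.

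**What to change.** In the secondary-analysis paragraph, or in the analysis plan with the protocol aligned to it:

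- State fixed effects for arm, time and arm-by-time, with a random patient intercept. Coding visit as categorical is a reasonable option but is not required.
- Name age and sex as adjustment covariates only.
- Make the between-arm difference in change from baseline at months 3, 6, 9 and 12, with its confidence interval, the treatment comparison.
- Name the factor in the analysis of variance, or drop that step if the mixed model replaces it.
- Describe the paired tests as descriptive within-arm results.

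The cost is a few sentences, with no new data, visits or patients. The change is best made before the first interim analysis (n=44).

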### Sample size

Sample size calculation was performed according to the sequential design method in order to consider the implementation of three interim efficacy analyses. The sample size was calculated with SAS applying the SEQDESIGN procedure, considering the risk of increasing the alpha risk due to multiple analyses. The method used in our case was the O’Brien-Fleming type of boundary (design method=obf) to maximise our chance of stopping the study at the final analysis, if we cannot reach a positive conclusion during the interim analyses.

The criteria applied for the sample size calculation were a total alpha risk at 0.025, with an estimated result of 75% remission in the personalised arm (number of rituximab doses defined by the algorithm) versus 50% in the standard arm (rituximab 1 g×2) and a one-sided sample test for the difference between two binomial proportions. These assumptions about remission rates are based on observations from a retrospective cohort comparing remission rates in patients with rituximab underdosing with those in patients without rituximab underdosing.^10^

Finally, to maintain the total alpha risk at 0.025 and the total beta risk at 0.2 with four analyses, we need to enrol 130 patients in our study, which accounts for a 5% rate of lost to follow-up (anticipated as minor in this study as patients are intensively followed for this pathology).

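### No between-arm comparison is specified for the secondary change endpoints: the paired tests and the mixed model, as written, contain no treatment-arm term

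*Protocol article*

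**What the plan says.** The Design section sets a two-arm superiority question: "This is a parallel, two-arm, randomised, open-label, multicentre (13 sites in France), prospective study comparing the superiority and safety" of the two regimens. Evaluation criteria lists, among the secondary endpoints, changes from baseline to months 3, 6, 9 and 12 in proteinuria and albuminuria, in serum creatinine and eGFR, and in anti-PLA2R1 titre.

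Statistical methods then gives the analysis of these endpoints in three parts:

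- **First step.** "Changes in biological samples at 3, 6, 9 and 12 months will be evaluated first by analysis of variance", if normality holds. No factor is named.
- **Second step.** A paired t-test or a Wilcoxon signed-rank test.
- **Longitudinal analyses.** A "linear mixed model to account for repeated measures, including fixed effects for time and intercept random effects for patients". The next sentence adds: "The variables of interest and adjustment will be primarily age and sex".

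The treatment arm is not mentioned in any of the three. The same section does state a comparison of the two groups for the primary endpoint, and a test for the difference between two proportions for complete and partial remission at month 12.

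**The concern.** Every patient in this trial receives rituximab. Proteinuria and antibody titre are expected to fall in both arms, so a demonstration that they fall says nothing about whether dosing by the algorithm is better than two fixed infusions. That question needs a contrast between arms.

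The trial has no matching of patients across arms, so the only natural pairing is a patient with himself or herself. The paired tests are therefore before-and-after tests. The mixed model has time, a patient intercept, age and sex. Its time effect is the course averaged over both arms, and no coefficient in it measures the regimen.

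If the analyses are run as written, the report on these endpoints can show convincing p-values with no arm effect behind them, or miss an arm effect that is present. The secondary laboratory endpoints would then neither support nor weaken the primary result.

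**Working it through.** **The plan's own figure.** The plan gives no sample size or power for the change endpoints. Its only sample-size figure is for the primary endpoint: 75% against 50%, one-sided alpha 0.025, beta 0.2, four looks, 5% loss. It reproduces:

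- Fixed design, per arm: (1.960 + 0.842)² × 2 × 0.625 × 0.375 / 0.25² = 58.9.
- With the O'Brien-Fleming inflation factor of 1.0242: 2 × 58.9 × 1.0242 = 120.6.
- After loss: 120.6 / 0.95 = 126.9, against the stated 130.

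This has no bearing on the point, except that it sets a realistic number per arm: 130 × 0.95 / 2 = 61.75, about 62.

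**What each named analysis estimates.** Let δC and δE be the true mean changes from baseline to a given visit in the control and experimental arms. With 1:1 allocation:

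| Analysis | Quantity estimated |
|---|---|
| ANOVA | not determinable, because no factor is stated |
| Paired test, all patients | (δC + δE)/2 |
| Mixed model with time, age, sex, patient intercept | (δC + δE)/2, through the time effect |
| What the trial asks | δE − δC |

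The average does not determine the difference. An average change of −1 fits δC = δE = −1 (difference 0) as well as δC = −0.5 and δE = −1.5 (difference −1).

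**Illustration.** All values here are assumptions and none comes from the protocol. There are 62 patients per arm and visits at months 0, 3, 6, 9 and 12. The between-patient SD and the residual SD are both 0.7, so the total SD is √(0.7² + 0.7²) = 0.99. Change is linear in time. Tests are two-sided at 5%, with 200 replicates. Changes are those at month 12. Entries are the percentage of runs that were significant.

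| δC, δE | Average | Difference | Paired test | Time-only model | Two-sample test of change | Time-by-arm model |
|---|---|---|---|---|---|---|
| −1, −1 | −1 | 0 | 100 | 100 | 3.5 | 7.5 |
| −1, −1.5 | −1.25 | −0.5 | 100 | 100 | 78 | 84.5 |
| +0.5, −0.5 | 0 | −1 | 3.0 | 4.5 | 100 | 100 |

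In the first row the between-arm results should be near 5%. The simulation standard error is √(0.05 × 0.95 / 200) = 1.5 percentage points, so 3.5 and 7.5 are compatible with that. The first two rows show that the paired test and the time-only model give the same result whether or not the arms differ. The third shows that they can miss a large difference. That row is a limiting case to make the point; opposite changes are not expected in this trial.

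**The case against.** The strongest reply is that the text is silent about arm and does not exclude it.

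- **The ANOVA.** It is the first-named method and its factor is not given. In a two-arm trial the factor could be arm. This stands. A reader might infer that none of the secondary change analyses compares the arms; the document does not support that for the ANOVA. The supportable statement is that no between-arm comparison is specified.
- **Open lists.** The model is described with *including* and the variables with *primarily*, and neither word closes the list. This article condenses a longer protocol, and an analysis plan not shown here may add arm. This stands in part. Full covariate lists are ordinary analysis-plan detail. But the article does list the model terms and does name the variables of interest, and the treatment is not among them. The paired test is a stated method that cannot answer the between-arm question, whatever is added to the model.
- **Baseline.** The missing baseline covariate is not an error in itself. A repeated-measures model can carry baseline as its first time point, and nothing in the text prevents that.
- **False claims from separate tests.** A reader might infer that the paired tests will be run within each arm and produce a spurious finding in one arm only. The text does not say that they are run by arm. The size of that risk also depends on an assumed power. With equal true change, the two arms disagree in 2 × 0.5 × 0.5 = 50% of trials at 50% power per arm, in 2 × 0.8 × 0.2 = 32% at 80%, and in 2 × 0.99 × 0.01 = about 2% at 99%. With a large response in both arms the last figure may be the closest, so this is not a measure of the problem.

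**Conclusion.** The point holds for the secondary change and longitudinal endpoints. As written, the paired tests and the mixed model do not estimate the effect of the algorithm-guided regimen, and the ANOVA is undetermined because its factor is not stated. That conclusion rests on reading the named terms as the ones that will be fitted; an analysis plan that adds arm would answer it for the model.

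No figure in the protocol changes. The illustrated rates depend on assumed variances and effects and show the direction of the failure, not its frequency in this trial.

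A reader might infer that the superiority claim of the trial is at risk. It is not: the primary endpoint and the month-12 complete and partial remission rates have stated between-arm tests. The correction should be made, but it concerns supporting evidence only.

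**What to change.** In Statistical methods, for the change and longitudinal secondary endpoints:

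1. Specify one linear mixed model per outcome on all randomised patients, with arm, visit and arm-by-visit as fixed effects and a random patient intercept. Age and sex may stay as adjustment variables, but arm should be named as the variable of interest.
2. Preferably bring in the baseline value of the outcome, as a covariate or as the first time point, and say which.
3. Report the arm difference with a 95% CI at months 3, 6, 9 and 12.
4. State the factor of the analysis of variance, or drop that step in favour of the model.
5. Keep the paired tests as descriptive only.

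The cost is wording in the protocol or the analysis plan. The visits, measurements and sample size stay the same. The change is best made before any outcome data are examined by arm, so before the first interim analysis at n=44.

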### Inclusion criteria

Patients will be recruited if they fulfil the following criteria: age ≥18 years; membranous nephropathy diagnosed by either the presence of circulating anti-PLA2R1 or anti-thrombospondin type-1 domain-containing 7A (THSD7A) antibodies or kidney biopsy; active nephrotic syndrome defined by proteinuria >3.5 g/24 hours (or urine protein-creatinine ratio >3.5 g/g) and serum albumin <30 g/L at screening; estimated glomerular filtration rate (CKD-EPI formula) >30 mL/min/1.73 m^2^; indication for rituximab treatment according to the 2021 KDIGO and French guidelines; non-immunosuppressive antiproteinuric treatment at a stable dose for 2 weeks, including a renin-angiotensin-aldosterone system inhibitor, a diuretic and a low-salt diet at the maximum tolerated dose (ie, absence of orthostatic hypotension and no increase in serum creatinine >30%); social insurance; and signed informed consent (online supplemental file 1). Women of childbearing age must use an effective method of contraception up to 12 months after the last rituximab dose is received.

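### The random patient intercept, the only within-patient dependence named for the longitudinal model, implies equal variance and correlation at all visits if residuals are independent, so visit-specific standard errors can be wrong in either direction

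*Protocol article*

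**What the plan says.** In the protocol article, the Statistical methods section states: "For longitudinal analyses, secondary outcomes will be analysed using a linear mixed model to account for repeated measures". It describes that model as "including fixed effects for time and intercept random effects for patients", so that "intercept random effects for patients" are the only within-patient dependence named, and adds: "The variables of interest and adjustment will be primarily age and sex". It mentions neither the residual covariance nor the type of standard error.

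The same paragraph gives a second route for the same measurements: "Changes in biological samples at 3, 6, 9 and 12 months will be evaluated first by analysis of variance", followed by paired t or Wilcoxon tests.

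The Evaluation criteria section defines the repeated endpoints as changes from day 0, for example "changes in proteinuria and albuminuria from baseline to month 3, month 6, month 9 and month 12". The Inclusion criteria section requires "proteinuria >3.5 g/24 hours (or urine protein-creatinine ratio >3.5 g/g) and serum albumin <30 g/L at screening".

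**The concern.** A random intercept with independent, equal-variance residuals gives compound symmetry: the same variance at each visit, and the same correlation between any two visits whether 3 or 12 months apart. Two features of this trial make that doubtful.

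- **Truncated baseline.** The entry criteria cut off proteinuria from below and albumin from above at screening, so the baseline spread need not match the later spread.
- **Divergence after treatment.** The Sample size section plans on 50% and 75% remission. Patients therefore separate after baseline, and correlation with the day-0 value can be expected to weaken over time.

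If the assumption fails, the model averages the variances and covariances over visits. A contrast at one visit then carries a standard error that belongs to no visit in particular. At stake are the tests and intervals for proteinuria, albumin, creatinine, eGFR and antibody titre at individual visits. Some would reject too often and others too rarely.

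**Working it through.** **Inputs.** The article gives the visits (day 0, months 3, 6, 9, 12) and 1:1 allocation. It gives no SD, correlation or standard error for any repeated outcome, so there is no figure of its own to reproduce. All SD and correlation patterns below are assumptions. The calculation also assumes complete, balanced data and a model with arm-by-visit means, although the article names no arm term.

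**Formulas.** Let V be the true 5×5 covariance matrix over the visits, with n patients per arm.

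- The fitted random-intercept model estimates the variance as the mean diagonal of V (call it T) and the covariance as the mean off-diagonal (call it C).
- Model variance of the arm difference in change from day 0: 2 × 2(T − C)/n, the same at every visit.
- True variance at visit k: 2(Vkk + V00 − 2V0k)/n.
- SE ratio (model/true) = √[2(T − C)/(Vkk + V00 − 2V0k)]; n cancels.
- Actual error of a nominal two-sided 5% test = 2[1 − Φ(1.96 × ratio)].

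**Worked example.** SDs 4/5/6/7/7; correlation 0.8 between adjacent visits, decaying as a power of distance.

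- T = (16 + 25 + 36 + 49 + 49)/5 = 35.0; C = 22.12; 2(T − C) = 25.77.
- Month 3: 25 + 16 − 2(16.00) = 9.00; ratio √(25.77/9.00) = 1.69; error 0.1%.
- Month 6: 36 + 16 − 2(15.36) = 21.28; ratio 1.10; error 3.1%.
- Month 9: 49 + 16 − 2(14.336) = 36.33; ratio 0.84; error 9.9%.
- Month 12: 49 + 16 − 2(11.469) = 42.06; ratio 0.78; error 12.5%.

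A simulation of 150 trials of 130 patients with this covariance gave 0, 3.3, 8.7 and 12.0%. That confirms the algebra, not the assumed covariance.

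**Other patterns, change from day 0.**

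| Correlation | SD pattern (day 0 to month 12) | SE ratio M3/M6/M9/M12 | Error %, M3/M6/M9/M12 |
|---|---|---|---|
| 0.8 per 3 months | rising 1.0 to 1.6 | 1.62/1.11/0.88/0.75 | 0.2/3.0/8.4/14.2 |
| 0.8 per 3 months | equal | 1.31/0.98/0.84/0.76 | 1.0/5.5/10.0/13.4 |
| 0.8 per 3 months | falling 1.6 to 1.0 | 1.15/0.89/0.79/0.75 | 2.4/8.1/12.0/14.2 |
| 0.8 per 3 months | hump 1/1.5/1.5/1.3/1.1 | 1.18/0.94/0.93/0.95 | 2.1/6.6/6.8/6.3 |
| 0.6 per 3 months | rising | 1.49/1.09/0.92/0.82 | 0.3/3.2/7.1/10.9 |
| 0.6 per 3 months | equal | 1.22/0.96/0.87/0.83 | 1.7/5.9/8.8/10.5 |
| 0.6 per 3 months | falling | 1.06/0.87/0.82/0.82 | 3.8/8.7/10.6/10.9 |
| 0.6 per 3 months | hump | 1.17/0.96/0.96/1.01 | 2.2/6.1/5.9/4.7 |
| constant 0.6 | equal | 1.00 throughout | 5.0 throughout |
| constant 0.6 | falling | 0.88/0.91/0.93/0.94 | 8.4/7.4/6.8/6.5 |
| constant 0.6 | hump | 0.98/0.98/1.12/1.26 | 5.4/5.4/2.9/1.4 |

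With the 4/5/6/7/7 pattern and decay of 0.6, month 12 is 9.3%. Across the rising, equal and falling patterns with decay 0.6 to 0.8, month 12 therefore runs from 9.3 to 14.2% and month 3 from 0.1 to 3.8%. Outside that range of decay, month 12 is 8.0 to 9.6% at 0.5 and 14.8 to 16.6% at 0.9.

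**Level at a visit instead of change.** The ratio is √(T/Vkk). Rising SD gives 1.15/1.01/0.91/0.82 at months 3/6/9/12; falling SD gives 0.91/1.01/1.15/1.32, the opposite direction.

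**The case against.** The strongest case against has four parts.

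1. **The text does not exclude a richer structure.** It says the model includes a random intercept, not that it contains nothing else. Serially correlated residuals, visit-specific variances or robust standard errors would all fit the sentence, and an analysis plan that is not shown may set them. This stands as a limit on the wording. The article nevertheless names one dependence structure, and its plain reading is compound symmetry, so the point concerns a stated method and not just a missing detail.

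2. **The direction of the error is unknown.** A reader might infer that intervals will be too wide at month 3 and too narrow at months 9 and 12. The documents do not support that as a fact, since it needs SDs and correlations they do not give. Truncation and divergence show that the spread may change, not which way; if most patients remit, the spread of proteinuria could fall. What does hold is narrower: for change from baseline with decaying correlation, that direction appears for rising, flat and falling SDs alike, but not for the hump-shaped SD at month 12 or, in general, under constant correlation.

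3. **The error rates need an arm-by-visit model, and the article names only time, age and sex.** This is correct. The arm contrasts are assumed here, and the fix should state those terms.

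4. **The consequences are limited.** A reader might also infer that conclusions on durable remission are at risk. Month-12 remission is compared by a test of two proportions, which this covariance does not touch, and the biological changes also have the ANOVA and paired-test route. This stands.

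**Conclusion.** The concern holds in conditional form. If the residuals are independent with equal variance, the stated model assumes compound symmetry from day 0 to month 12, which this design gives reason to doubt. Its visit-specific standard errors can then err either way: over the patterns in the table, the ratio of model to true standard error for change from baseline runs from 0.88 to 1.62 at month 3 and from 0.75 to 1.26 at month 12.

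Under decaying correlation with rising, flat or falling SDs, the error at month 12 is about two to three times nominal and month 3 is conservative. Those figures rest entirely on assumed covariances, complete data and an added arm-by-visit term. A definite claim about direction, or high confidence in any single error rate, is not justified. The primary test, its significance levels and N=130 are unaffected.

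**What to change.** State the longitudinal model with arm, visit and arm-by-visit terms, the day-0 value as covariate, and an unstructured covariance across the four follow-up visits, fitted by REML with Kenward-Roger degrees of freedom. Name a fallback structure in case the fit does not converge.

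Alternatively, keep the random intercept with the same arm and visit terms and use robust standard errors clustered on patient. Either option removes the dependence on compound symmetry, whichever way the error would have run. The unstructured model is preferable if some visits are missing, because likelihood estimates under data missing at random rely on a correct covariance.

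The cost is a sentence or two in the analysis plan. Four follow-up visits need 4 × 5/2 = 10 covariance parameters, which is manageable with about 123 patients (130 × 0.95 = 123.5 after the planned 5% loss). The downside is those few extra parameters and the possible use of the fallback.
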